## Abstract

Poor intervertebral disc (IVD) health is associated with low back pain (LBP). This 12-week parallel randomised controlled trial will evaluate the efficacy of a progressive interval running programme on IVD health and other clinical outcomes in adults with chronic LBP. Participants will be randomised to either a digitally delivered progressive interval running programme or waitlist control. Participants randomised to the running programme will receive three individually tailored 30 min community-based sessions per week over 12 weeks. The waitlist control will undergo no formal intervention. All participants will be assessed at baseline, 6 and 12 weeks. Primary outcomes are IVD health (lumbar IVD T2 via MRI), average LBP intensity over the prior week (100-point visual analogue scale) and disability (Oswestry Disability Index). Secondary outcomes include a range of clinical measures. All outcomes will be analysed using linear mixed models. This study has received ethical approval from the Deakin University Human Research Ethics Committee (ID: 2022-162). All participants will provide informed written consent before participation. Regardless of the results, the findings of this study will be disseminated, and anonymised data will be shared via an online repository. This will be the first study to evaluate whether a progressive interval running programme can improve IVD health in adults with chronic LBP. Identifying conservative options to improve IVD health in this susceptible population group has the potential to markedly reduce the burden of disease. This study was registered via the Australian New Zealand Clinical Trials Registry on 29 September 2022 (ACTRN12622001276741).

WHAT IS ALREADY KNOWN ON THIS TOPICExercise training is known to improve a range of health-related outcomes (eg, pain intensity and disability) in adults with chronic low back pain.WHAT THIS STUDY ADDSThis randomised controlled trial will be the first to examine the safety and efficacy of a progressive interval running programme on intervertebral disc (IVD) health.HOW THIS STUDY MIGHT AFFECT RESEARCH, PRACTICE OR POLICYThis study represents a critical step towards identifying a conservative treatment capable of improving IVD health in this susceptible population group.

## Introduction

Low back pain (LBP) is the leading cause of age-standardised disability worldwide and affects approximately 7.1% (568.4 million) of the global population.^1^ Annual healthcare expenditure associated with LBP is more than US$134.5 billion in the USA^2^ and $A9 billion in Australia.^3^ Given that as much as 85% of LBP healthcare expenditure stems from chronic LBP (CLBP; ≥12 week pain duration),^4^ identifying effective management strategies is vital.

We previously showed via a network meta-analysis^5^ that exercise training effectively reduces pain intensity and disability in adults with CLBP. However, only some types of exercise training (eg, Pilates, motor control exercises and resistance training) resulted in clinically meaningful improvements in both pain intensity and disability.^6^ These types of exercise training primarily target paraspinal musculature, which suggests improving spinal tissue health can reduce pain intensity and disability.^6^ However, limited studies to date have examined the effect of exercise training on other spinal tissues, such as the intervertebral disc (IVD).

A meta-analysis of 14 studies (3097 participants)^7^ showed individuals with MRI-derived markers of poor IVD health (eg, IVD bulge, degeneration, extrusion or protrusion) were up to eightfold more likely to have LBP. Poor IVD health may lead to surgery associated with additional risks and high financial costs.^8 9^ Identifying conservative interventions that improve IVD health in adults with CLBP is critical for reducing individual and healthcare burdens.

We previously conducted the first exercise training randomised controlled trial designed to assess the possibility of improving IVD health in adults with CLBP.^10^ The intervention group received 6 months of combined resistance and cardiovascular exercise training (two 60 min supervised sessions per week) designed to mechanically stress IVDs. The control group also received treatment (motor control exercises and manual therapy), designed to minimise exercise-related mechanical stress to IVDs. While no between-group differences in IVD health were observed, exercise training led to within-group changes in two MRI-derived markers of IVD health: (1) IVD T2 and (2) IVD height expansion in short-duration lying. Both of these observations indicated that exercise training might be viable for improving IVD health,^11^ yet the lack of between-group difference suggests different types of exercise training require investigation.

Building on our prior data,^12^ we identified that a history of cardiovascular exercise training,^13^ and specifically cardiovascular exercises performed in an upright posture (eg, running, rather than swimming or cycling),^14^ were associated with better IVD health. Our observations support that improving IVD health appears contingent on the type of exercise training provided. Similar to how impact exercise training (eg, jumping) is required to improve bone health,^15^ cardiovascular exercise training in an upright posture (eg, running) appears integral to improving IVD health.^11^ Therefore, the primary aim of this 12-week single-blind (researchers) two-arm parallel individually randomised controlled trial is to determine the efficacy of a progressive interval running programme on IVD health, pain intensity and disability in adults with CLBP. The secondary aims are to determine intervention feasibility and efficacy across a range of subjective and objective health-related outcome measures.

## Methods

### Study setting

Data will be collected in a dedicated room at an imaging facility (Imaging @ Olympic Park, Melbourne, Australia), at a commercial pathology clinic collection centre (Melbourne Pathology, Melbourne, Australia) and via an online questionnaire (REDCap, Nashville, USA).^16 17^ The intervention will be conducted within the community of the participants.

### Patient and participant involvement

Patient and participant involvement will be planned, recorded and evaluated throughout the trial according to the Guidance for Reporting Involvement of Patients and Public shortform checklist.^18^

### Eligibility criteria

We will recruit a sample of 40 adults (18–45 years) with non-specific (no known specific pathology) chronic (>12 weeks) LBP (pain located between the costal margin and above the inferior gluteal folds, with or without leg pain and experienced on most days in an average week). Exclusion criteria will consist of: (a) history of spinal surgery, spine trauma (eg, fracture or car accident), cauda equina symptoms, known structural scoliosis requiring surgical consultation, symptomatic radiculopathy (diagnosed via medical professional or leg pain greater than back pain), inflammatory spondyloarthropathies or non-musculoskeletal causes of LBP (eg, infection), (b) inability to communicate in English, (c) pregnancy, lactating or less than 1-year postnatal, (d) current or prior elite athletes (eg, member of Australian Institute of Sport, State Institutes or Academies of Sport or the national squad of any sport),^19^ (e) any absolute contraindications for MRI, (f) any absolute contraindications for exercise training, (g) participation in running or sport that involves running in the last 3 months (>1 session per month), (h) having experienced a lower limb injury in the last 6 weeks, (i) deemed higher risk of adverse event due to physical activity per the Adult Pre-Exercise Screening System^20^ and (j) unable to access a smartphone with a cellular internet connection.

### Interventions

#### Exercise training

The exercise training will consist of three community-based 30 min sessions per week for 12 weeks prescribed by an accredited exercise physiologist from the research team. Exercise training sessions will be individualised based on information during a 30 min initial assessment completed at Imaging @ Olympic Park. Exercise training sessions will consist of a 5 min general warm up followed by an interval-based running programme that will be progressed weekly as guided by an accredited exercise physiologist from the research team. The programme for each participant will be delivered and monitored through the RunKeeper application (ASICS Runner App, Boston, USA), using a preallocated study code allowing for deidentified tracking of running speed, distance and surface (ie, grass, gravel, paved, trail or mixed). Participants will receive educational content delivered via REDCap throughout the intervention covering the following topics: (a) ideal running speed, (b) footwear selection, (c) the safety of running and (d) dealing with setbacks (online supplemental appendix A). Participants will initially meet for 15 min weekly (weeks 1–4) and then fortnightly (weeks 6–12) via secure video consultation (Zoom Video Communications, California, USA) with a member of the study team to discuss the exercise training programme.

10.1136/bmjsem-2022-001524.supp1Supplementary data

The exercise programme will consist of short running intervals interspersed with rest periods of walking (table 1). This interval-based training is an effective way to increase running capacity in untrained novice runners^21^ and is recommended following hip and lower limb injuries to safely return to running.^22–24^ Participants enter the interval training programme at stage 1, 2 or 3 as determined by a 2 min running tolerance test at the initial physical assessment. During this run test, participants will be instructed to run at a slow to moderate pace for as long as they are comfortable, up to a maximum of 2 min. Participants who can complete the slow run comfortably for: (a) 0–44 s will start at stage 1 of the programme; (b) 45–89 s will start at stage 2 of the programme; and (c) 90–120 s will start at stage 3 of the programme. Participants may choose their starting point (stage 1, 2 or 3) in consultation with the accredited exercise physiologist, irrespective of the test results. At each stage, participants can self-select their chosen number of repeats to complete based on their overall perceptions of exertion, breathlessness and pain intensity. For example, at stage 2, participants can select to complete between 6 and 10 repeats of 30 s running. This approach accounts for the daily fluctuations in pain intensity observed in up to 35% of individuals with CLBP^25^ while promoting self-efficacy through autonomy and shared decision-making.^26^ Once participants complete the upper repeat range each week, they progress to the next stage. To reduce the risk of injury due to the rate of progression, participants can only increase one stage per week and must complete at least two sessions per week before progressing to the following stage.^22^ The increase in average running time per week (table 1) is greater over the first 6 weeks and reduces throughout the programme. This is due to a conservatively chosen starting point to facilitate confidence with running, facilitate familiarity with sensations associated with muscle fatigue and reduce the interference of possible fatigue-related pain interpreted as injury pain. For example, the graded exposure to running commences at 1.5 min total running time per session at stage 1, progressing by 20%–100% over the first 6 weeks before levelling off to increases of approximately 10%–15% after that. Importantly, in novice runners, there is no difference in the prevalence of running-related injuries between training programmes that adhere to a strict 10% weekly increase and those that include greater weekly progressions of up to 50%.^27^ If participants reach the final stage before the end of the intervention, they will stay in this stage for the remaining weeks. Throughout the intervention, participants will be advised to run at a slow to moderate pace (maximum of 10 km per hour or 6 min per km), which corresponds with velocities thought to have a positive stimulus on the IVD.^12^ In collaboration with the accredited exercise physiologist, participants can regress to an earlier stage of the interval programme if deemed necessary (eg, significantly increased LBP, other injuries/soreness, following periods of poor adherence).

**Table 1 T1:** Interval training programme

Stage	Run interval (s)	Walk interval (s)	Repeats		Total session time (min)		Total running time per session (min)		Total running time per week (min)	Increase in weekly running time from the previous week
			Lower	Upper	Minimum	Maximum	Minimum	Maximum		
1	15	120	6	10	13.5	22.5	1.5	2.5	4.5	NA
2	30	120	6	10	15	25	3	5	9	100.00%
3	45	115	6	10	16	26.7	4.5	7.5	13.5	50.00%
4	60	90	6	10	15	25	6	10	18	33.33%
5	75	75	6	10	15	25	7.5	12.5	22.5	25.00%
6	90	60	6	10	15	25	9	15	27	20.00%
7	105	45	6	10	15	25	10.5	17.5	31.5	16.67%
8	120	45	6	10	16.5	27.5	12	20	36	14.29%
9	135	45	6	8	18	24	13.5	18	40.5	12.50%
10	150	30	6	8	18	24	15	20	45	11.11%
11	165	30	6	8	19.5	26	16.5	22	49.5	10.00%
12	180	30	6	8	21	28	18	24	54	9.09%
13	210	15	6	8	22.5	30	21	28	63	16.67%

Determined by baseline testing, participants start at stage 1, 2 or 3 and progress to the next stage once they complete the upper repeat range. The total running time per week is calculated based on 3 weekly sessions at the lower repeat range.

NA, not applicable.

#### Waitlist control

Participants allocated to the waitlist control arm will be asked to manage their LBP per usual (eg, general practitioner management, over-the-counter pharmacotherapy) and avoid commencing a running programme. No formal intervention will be provided during the 12-week follow-up. Following completion of the study, waitlist participants will be offered the same exercise training programme and one-on-one consultation with an accredited exercise physiologist as per the intervention group.

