#### Habitual physical activity

The seven-item International Physical Activity Questionnaire will quantify habitual physical activity at baseline, 6 weeks and 12 weeks.^45^ The questionnaire asks about the frequency/duration of vigorous and moderate intensity physical activity, walking and sitting over the past 7 days. Total weekly physical activity will be calculated by weighting each type of activity by its energy requirement in metabolic equivalent to produce a score in metabolic equivalent minutes. The International Physical Activity Questionnaire has moderate to excellent test–retest reliability (ICC=0.70–1.00).^45^

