#### Activity-specific beliefs

A six-item questionnaire will be used to assess the beliefs of safety towards specific physical activities at baseline, 6 weeks and 12 weeks. Questions one to four relate to the current and past involvement in a range of physical activities, while questions 5 and 6 evaluate the belief in safety. Question six asks the respondent, ‘Do you think the following exercises/movements are safe for you to do?’ Responses to 20 common physical activities are rated on a five-point Likert scale from definitely no to definitely yes. A 10–15 s video accompanies each activity to provide respondents with a clear reference. For activities perceived as unsafe (responses of definitely no and probably no), two additional questions will explore the meaning of this belief and the subsequent impact this has on participation.

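### The waitlist instruction restricts less running than the entry criterion counts as running exposure, so some dilution of the contrast is permitted and no measure of running sessions or dose in controls is specified

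*Protocol article*

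**What the plan says.** Criterion (g) in the Eligibility criteria section of the protocol article excludes people with "participation in running or sport that involves running in the last 3 months (>1 session per month"). Running sport and unstructured running thus count as exposure at entry, with a frequency limit.

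The Waitlist control section says that controls "will be asked to manage their LBP per usual (eg, general practitioner management, over-the-counter pharmacotherapy") "and avoid commencing a running programme". It adds: "No formal intervention will be provided during the 12-week follow-up". Neither running sport nor informal running is named. The only other activity limit in the article is under Lumbar spine MRI. It rules out strenuous activity or sport on the day of scanning and applies to all participants.

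The Introduction gives the primary aim as "to determine the efficacy of a progressive interval running programme on IVD health, pain intensity and disability in adults with CLBP". The reason offered is that "cardiovascular exercise training in an upright posture (eg, running) appears integral to improving IVD health".

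Two instruments record activity in both arms at baseline, 6 and 12 weeks. Of the International Physical Activity Questionnaire (IPAQ), the Habitual physical activity section says: "The questionnaire asks about the frequency/duration of vigorous and moderate intensity physical activity, walking and sitting over the past 7 days". Of the other, the Activity-specific beliefs section says: "Questions one to four relate to the current and past involvement in a range of physical activities". The individual items are not printed.

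**The concern.** The protocol uses a broad definition of running exposure to choose participants and a narrower one to restrict controls. Someone who enters with no recent running, is allocated to the waitlist and then joins a weekly football game or starts jogging without a plan has followed the instruction. If kept up, the same habit would have met criterion (g).

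The trial compares a running programme with none. If some controls acquire part of the same loading, the intention-to-treat difference moves towards zero for T2, pain and disability. The analysis rightly keeps those controls in their allocated group, so the safeguards are a clear instruction and a record of what controls did. This matters for reading a null result. The Introduction reports that the team's earlier exercise trial found no between-group difference in disc health.

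**Working it through.** The article states no contamination figure, so there is none to reproduce. The check is a comparison of text, followed by an illustration of size.

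**1. Definition of exposure, by stage**

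| Stage | What is covered | Where |
|---|---|---|
| Entry | Running, or sport that involves running, above one session per month over 3 months | Eligibility criteria, (g) |
| 12-week control period | Starting a running programme | Waitlist control |
| Scan day, all participants | Strenuous activity or sport | Lumbar spine MRI |

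Informal running and running sport appear in the first row and drop out of the second.

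**2. What would record running in controls**

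- RunKeeper tracking is described only for the exercise programme (Exercise training).
- IPAQ covers intensity classes, walking and sitting over 7 days. It could show a rise in vigorous activity but not identify it as running, and it leaves most of each 6-week interval unobserved.
- The bone-specific activity history is taken at baseline only (Table 2).
- The fortnightly video consultations are described for the exercise arm only (Feasibility; Adverse events).
- The activity-beliefs questionnaire asks both arms about current activities at 6 and 12 weeks, so it may reveal new running or sport. Whether it counts sessions cannot be told from the article.

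**3. Dose under test**

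Table 1, at the lower repeat range and three sessions a week, gives 3 × 1.5 = 4.5 min of running per week at stage 1 and 3 × 21 = 63 min at stage 13. Recreational running or field sport could plausibly reach part of that range.

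**4. Possible dilution**

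Inputs from the Sample size section: targets of 5.1 ms (T2), 20 (pain) and 10 points (disability), with 20 per group. Assumed: a share c of controls takes up running, and each gains a fraction g of the programme effect.

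Expected difference = target × (1 − c × g). With g = 1, the upper bound for each c:

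| c | Controls of 20 | T2 (ms) | Pain | Disability |
|---|---|---|---|---|
| 5% | 1 | 5.1 × 0.95 = 4.8 | 19 | 9.5 |
| 10% | 2 | 5.1 × 0.90 = 4.6 | 18 | 9 |
| 20% | 4 | 5.1 × 0.80 = 4.1 | 16 | 8 |

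At the same variance and power, the required sample size grows by about 1/(1 − c)²: 1.11, 1.23 and 1.56 respectively. With g = 0.5, c = 10% gives 5.1 × (1 − 0.05) = 4.8 ms, the same as the first row.

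The planned total makes no allowance for this: 28/(1 − 0.30) = 40, so the inflation covers attrition only.

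**The case against.** The strongest reply is that nothing here conflicts. Criterion (g) selects people without recent running, and the waitlist instruction stops controls from starting the kind of intervention under test. The two rules serve different purposes and need not share wording. The stated aim concerns a structured programme against usual management, so incidental activity could be seen as part of the comparator. That stands: a reader might infer a contradiction, and the documents do not support one.

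A reader might also infer that controls are free to take up the very exposure being tested. That goes too far. The Exercise training section specifies graded intervals with a pace ceiling tied to velocities thought to benefit the disc, and the article attributes no equal effect to football or jogging. What remains is that the stated rationale concerns upright loading, which running sport shares in part.

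A third inference is that running in controls goes wholly unmeasured, so that a null result could not be interpreted. The activity-beliefs questionnaire prevents that conclusion.

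Uptake may also be low. Participants have pain on most days and have run little or not at all for 3 months, and controls are offered the programme afterwards. Finally, the participant form (online supplemental appendix D) is not shown and may carry a wider instruction. These replies limit the size and tone of the point. They do not remove the gap between the two wordings.

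**Conclusion.** The point holds as a cheap improvement. The control restriction, as the article states it, is narrower than the protocol's own definition of running exposure, and it permits behaviour that could pull all three primary contrasts towards no difference. The article specifies no measure of running sessions or dose in controls, although existing items may show current running or sport.

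The size is unknown. At 5% to 10% uptake the loss is at most 0.3 to 0.5 ms for T2, 1 to 2 points for pain and 0.5 to 1 point for disability. At 20% it is at most 1.0 ms, 4 points and 2 points. These figures rest on assumed rates and on each such control gaining the full programme effect, so they bound the loss at each rate and do not predict it.

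**What to change.** - Reword the Waitlist control section so that, for the 12 weeks, controls are asked not to take up running or sport that involves running beyond the limit already in criterion (g). This asks them only to stay as they were at entry.
- Reconcile that wording with the participant information and consent form.
- Check whether the activity-beliefs items capture the number of running and running-sport sessions at 6 and 12 weeks. If they do not, add one REDCap item in both arms on sessions outside the study programme since the last visit.
- Report control-arm running exposure, by the criterion (g) definition, beside the intention-to-treat result.

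The cost is one phrase, at most one extra item at two existing visits, and a slightly wider request to controls. The change can go through the registry update route in the Protocol amendments section.
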